## Abstract

**Background:**

Supportive educational programs during the perinatal period are scarce in Singapore. There is no continuity of care available in terms of support from community care nurses in Singapore. Parents are left on their own most of the time, which results in a stressful transition to parenthood. There is a need for easily accessible technology-based educational programs that can support parents during this crucial perinatal period.

**Objective:**

The aim of this study was to describe the study protocol of a randomized controlled trial on a technology-based supportive educational parenting program.

**Methods:**

A randomized controlled two-group pretest and repeated posttest experimental design will be used. The study will recruit 118 parents (59 couples) from the antenatal clinics of a tertiary public hospital in Singapore. Eligible parents will be randomly allocated to receive either the supportive educational parenting program or routine perinatal care from the hospital. Outcome measures include parenting self-efficacy, parental bonding, postnatal depression, social support, parenting satisfaction, and cost evaluation. Data will be collected at the antenatal period, immediate postnatal period, and at 1 month and 3 months post childbirth.

**Results:**

Recruitment of the study participants commenced in December 2016 and is still ongoing. Data collection is projected to finish within 12 months, by December 2017.

**Conclusions:**

This study will identify a potentially clinically useful, effective, and cost-effective supportive educational parenting program to improve parental self-efficacy and bonding in newborn care, which will then improve parents’ social support–seeking behaviors, emotional well-being, and satisfaction with parenting. It is hoped that better supported and satisfied parents will consider having more children, which may in turn influence Singapore’s ailing birth rate.

**Trial Registration:**

International Standard Randomized Controlled Trial Number (ISRCTN): 48536064; https://www.isrctn.com/ISRCTN48536064 (Archived by WebCite at http://www.webcitation.org/6wMuEysiO)

## Introduction

### Background

The addition of a newborn to a family unit necessitates an environment of change and uncertainty [1] as parents are confronted with various new challenges and struggle to adapt to the new dynamics at home [2]. The parenthood experience is largely influenced by many factors including parents’ confidence levels, emotional well-being, social networks, and the quality of their support system [3]. Such environmental factors are capable of acting as a security blanket to buffer against the stressors that comes with parenthood, or add on to the stress parents are already facing, and such negative experiences can deter couples from becoming parents again. It is crucial to maintain positive emotional well-being in parents as studies have shown that maternal psychosocial stress can influence dynamics in the family [4-6].

In view of the dipping fertility rate [7,8], the Singapore government has been coming up with attractive incentive packages [9-11]; however, these have proven to be futile in boosting fertility rates. Low fertility rates are associated with multiple factors including an economic drain [12], parental expectations of childbirth, and previous negative birth experiences [13,14]. Previous studies have found that perinatal experiences were one of the major factors affecting birth rate [15,16]. Negative perinatal experiences such as a lack of support during this crucial period may influence a parent’s decision to give birth again [17]. In Singapore, perinatal support is mainly provided by maternity hospitals [18]. Unlike certain parts of Western Europe, continuity of care post hospital discharge by community care nurses is lacking in Singapore [19].

To assist parents in transiting smoothly into parenthood, antenatal classes and postnatal educational sessions are available at the hospitals in Singapore [20]. However, because of early discharges [21] and having so much to teach, parents are overloaded with too much information [22], which limits the effectiveness of these educational sessions. In a local study, mothers found that informational support provided by the hospital was unsatisfactory [20] as the most crucial period for parents is usually the first few weeks post discharge, when parents are left to handle stressful situations on their own. Moreover, current perinatal services in Singapore focus much of their attention on supporting women’s transition to early motherhood during hospitalization and pay less attention to fathers. A study conducted in Canada revealed that fathers did not feel supported by the hospital environment with regard to promoting their involvement with their newborn [23]. Therefore, there is a need for a theory-based educational program that focuses on facilitating smooth transition to parenthood for both parents.

Previous local studies were mainly focused on first-time mothers [24] or the early postpartum period [25]. There is a limited amount of educational programs that are developed for both first-time and experienced parents across the perinatal period. Support for parents from the antenatal period until the postnatal period is recommended in both international [26-28] and local [25] studies. Additionally, most of the available educational programs are delivered face-to-face, in which information is relayed didactically [27,29]. The shortage of midwives and nurses limits the feasibility of such programs as they are not cost-effective [29].

With the advancement in technology, the use of technology-based educational programs with new parents during the postnatal period both internationally [22,30,31] and in local context [25] have found to be successful in influencing parental outcomes in the postnatal period. However, because of the lack of a rigorous experimental study design [22,31] and limited postnatal focus [25,30,32], there is a need to develop an intensive family-oriented perinatal educational program that is professionally based and provided at a low cost, utilizing technology to enhance accessibility to all parents without compromising its effectiveness on parental outcomes. As such, this study aims to develop a technology-based supportive educational parenting program (SEPP) to support both fathers and mothers across the perinatal period by targeting different variables through the different components of the SEPP.

### Theoretical Framework

The theoretical framework guiding the SEPP is Bandura’s self-efficacy theory and Bowlby’s attachment theory [32,33]. According to Bandura’s self-efficacy theory [33], parenting self-efficacy (PSE) is considered one of the major determinants of competent parenting and the well-being of a newborn and is related to parental emotional well-being such as postnatal depression and the social support available for parents. Bowlby also theorizes that early parent-to-infant attachment provides the foundation of psychological well-being and, later, the development for infants in building social relationships, which can be influenced by PSE, emotional well-being, and social support [32]. Social support is associated with high PSE, which is in turn related to better emotional well-being and enhanced parental bonding with their newborn [24,27,34,35], which may ultimately lead to better parenting satisfaction. Hence, PSE, parental bonding, emotional well-being, and social support are interrelated variables, and the SEPP aims to target these variables to improve parental outcomes. This theoretical framework is represented in Figure 1.

### Aims

The aims of the study were to (1) examine the effectiveness of the SEPP on parental outcomes, including PSE (primary outcome), parental bonding, postnatal depression and anxiety, social support, and parenting satisfaction; (2) evaluate the cost-effectiveness of the SEPP compared with routine perinatal care; and (3) process evaluation of the SEPP by assessing its strengths and weaknesses from parents’ perspectives.

### Hypotheses

The hypotheses are (1) When compared with those in the control group receiving routine care, parents receiving the SEPP will report significantly (a) higher levels of self-efficacy in newborn care, (b) higher levels of parental bonding, (c) lower levels of depression and anxiety, (d) higher levels of social support received, and (e) higher levels of parenting satisfaction and (2) It is more cost-effective to provide the SEPP than routine care.

**Figure 1 figure1:**
[figure not shown]
Theoretical Framework showing interrelationship between outcome variables. SEEP: Supportive educational parenting programme; PSE: Parenting self-efficacy; PB: Parental bonding; PND: Postnatal depression; PS: Parenting satisfaction; SS: Social support.

## Methods

### Design

A randomized controlled two-group pretest and repeated posttest experimental design will be used. Couples (n=118 participants) recruited from a tertiary hospital will be randomly assigned into the two groups (intervention group receiving the SEPP and routine care or control group receiving only routine care). Data will be collected via questionnaire surveys using locally validated and reliable instruments, medical reviews, semistructured face-to-face interviews, and telephone interviews.

### Components of the Supportive Educational Parenting Program

Parents who are assigned to the intervention group will receive the SEPP and routine perinatal care provided by the hospital. Parents in the control group will receive only routine care. The routine care includes antenatal check-ups with an obstetrician and short postnatal stays in the hospital. During antenatal check-ups, the progress of the pregnancy is assessed via maternal bio-physiological profile, height and weight, and abdominal palpation. Antenatal educational classes are available; however, they are charged and not fully utilized by parents because of their lack of awareness [24]. During postnatal stay, parents will receive care from an obstetrician, nurses, and lactation consultants. Parent-craft educational classes are available. However, because of the short hospital stays, most of the parents are too tired to attend these sessions [24]. The SEPP consists of three main components, as presented in Table 1.

In Singapore, the mobile phone penetration rate was approximately 98% in 2016 [36], which is the highest globally. Moreover, under the smart nation initiative, Singapore is moving toward delivering holistic health care to the population through technological innovations [37]. Hence, delivering the SEPP in the form of a mobile health (mHealth) app is not only feasible but also a sustainable and convenient form of education delivery for health care professionals (HCPs) and parents. All educational contents in the app has been reviewed and approved by the ethics board.

**Table 1 table1:** Details of the Supportive Parenting Educational Program.

No.^a^	Mode and period of delivery	Approximate duration of the session	Topics covered
1	Telephone-based antenatal educational session	30 min	Parental self-efficacy and bonding (eg, definitions of parental self-efficacy and bonding, why are they important, and how they can be enhanced Expectations in the immediate postpartum period Emotional needs of parents both during pregnancy and after the child’s birth
2	Telephone-based immediate postnatal educational session	60 min	Reinforcement on the topics covered during antenatal period, including parenting self-efficacy, parental bonding, and postnatal depression Coverage on parent-craft class topics including baby bathing and breastfeeding Role of fathers during postnatal period
3	mHealth^b^ app-based follow-up educational session	1 month access to the mHealth app	A knowledge-based content on topics including newborn and maternal care Audio recordings of the knowledge-based content Videos on various newborn care tasks such as baby bathing and breastfeeding demonstrated by a trained midwife using a live baby. Each video is approximately 8 min long on average A discussion forum Push notifications

^a^Number in series.

^b^mHealth: mobile health.

The knowledge-based content in the mHealth app includes evidence-based information on ways to enhance parental self-efficacy and bonding, newborn care and maternal self-care tasks, emotional challenges and ways of dealing with it, breastfeeding-related information, and insights for new parents for a smooth transition to parenthood. The discussion forum will be a platform for parents to ask any questions they might have. All parental queries will be answered by a trained midwife (research assistant 1, RA1) once a day for the first 4 weeks post childbirth because this period is the most stressful period for new parents in the early post-partum period [38,39]. Additionally, other parents can also provide insights to these queries by sharing their personal experiences. According to Bandura’s self-efficacy theory [33], self-efficacy and a help-seeking behavior (social support) can be enhanced when tasks are learned from others in a similar situation; therefore, parents are encouraged to interact with other parents in the discussion forums. Daily push notifications regarding important milestones on parenting will be sent to users. Each notification appears on the user’s home screen, which aims to pique the user’s interest and serves as a reminder to continue exploring the rest of the content-rich app. Participants’ access to the mHealth app will be monitored (by adding the function of time spent in accessing materials) to record the dosage of the intervention each participants receives. The app was developed by an external vendor who is an expert in mHealth app development. The research team and the external app developer have been keeping in close contact for the development of the app. Screenshots of the features of the app as examples are shown in Figures 2-6.

To ensure consistency, the same RA (RA1) will deliver the telephone-based prenatal and postnatal educational component in the SEPP to all the participants in the intervention group. The protocol for the SEPP has been validated by an expert panel consisting of five HCPs (one nursing professor who is experienced in postnatal educational programs, one senior consultant-neonatologist, one senior consultant-obstetrician, and two experienced midwives in perinatal education) and two sets of parents.

**Figure 2 figure2:**
[figure not shown]
Screenshot of knowledge-based content.

**Figure 3 figure3:**
[figure not shown]
Screenshot of audio recordings.

**Figure 4 figure4:**
[figure not shown]
Screenshot of discussion forum.

**Figure 5 figure5:**
[figure not shown]
Screenshot of videos.

**Figure 6 figure6:**
[figure not shown]
Screenshot of push notifications.

Inclusion criteria.Are 21 years and aboveAre able to read and speak EnglishHave low-risk singleton pregnancy with more than 28 weeks of gestationHave a mobile phone with Internet accessPlan to stay in Singapore for the first 3 months post delivery

Exclusion criteria.Have self-reported physical or mental disorders that will interfere with their ability to participate in the studyHave high-risk pregnancy, including placenta-previa major, preeclampsia, and pregnancy-induced hypertensionHave complicated assisted delivery such as vacuum or forceps with 4th degree perineal tear of the motherGave birth to a stillborn or a newborn with congenital abnormalities or medical complications, orAre a single parent

### Participants

The participants recruited will be couples (a father and mother dyad is considered one couple). The inclusion and exclusion criteria for participants who are mothers are shown in Textboxes 1 and 2.

The inclusion criteria for fathers are those who (1) are 21 years and above, (2) are able to read and speak English, (3) have a mobile phone with Internet access, and (4) plan to stay in Singapore for the first 3 months post delivery. The exclusion criteria for fathers are those who have self-reported physical or mental disorders that will interfere with their ability to participate in the study and/or are a single parent.

All couples are recruited antenatally and will be told beforehand that they may be excluded from the study if mothers are to experience complication during their pregnancy and the delivery of their newborn.

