
### Study Procedure

The study consists of two phases: (1) planning intervention strategies for the intervention group, including the development of the educational content to be covered during the antenatal and postnatal periods and the development of the mHealth app, audio, and videos related to postnatal care, and (2) implementation of the SEPP and investigating its effectiveness on parental outcomes.

This study has been approved by the ethics board, and recruitment at the antenatal clinics has started at the study venue. The principle investigator and her team will inform nurse managers and clinicians at the antenatal clinics before a RA (RA1) commences the process of recruitment. Before contacting potential participants, the attending nurses and/or clinicians will be approached to assess each couple’s physical and psychological well-being before inviting them to participate in the research study. The referred couples will once again be assessed using the inclusion and exclusion criteria. There will be no undue influence or coercion used to recruit couples into the study. Each couple will be given details of the purpose of the study and ample time to ask questions and to consider before deciding to participate. It will be strongly emphasized that their participation is solely voluntary and that they may choose not to participate without any harm or compromise in the care they receive. Verbal and written consent will be obtained from the couple, both mother and father, thereafter. Both first-time and experienced mothers, regardless of their parity, who meet the inclusion criteria, along with their partners, will be recruited. RA1 will visit the antenatal clinics regularly to recruit participants according to the inclusion and exclusion criteria and will be responsible for randomizing the participants.

Once consent has been taken, demographic and baseline data of the participants will be obtained, and randomization will take place. In addition, recruited couples will be asked for their contact details so that they can be contacted for subsequent follow-ups. RA1 will keep in constant contact with the participants to ensure the birth of the newborn. For participants in the intervention group, telephone-based antenatal education session will be delivered by RA1 at the participants’ convenience at a prearranged timeslot.

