### Data Collection

A single-blind technique will be adopted, in which the RA (RA2) responsible for the collection of data post intervention or post discharge will not be aware of the treatment allocation, which will be conducted by another RA (RA1). RA2 will be responsible for the collection of all interim and postintervention data, including the process evaluation interviews. Outcome measures will take place at the following time points for all parents: (1) during pregnancy, before randomization (baseline); (2) after childbirth, before hospital discharge (interim data); (3) post intervention for the SEPP intervention group and at the end of week 4 post childbirth for the control group (posttest 1); and (4) 2 months after the SEPP for the intervention group and 3 months post childbirth for the control group (posttest 2). The period when parents are prone to facing various challenges is at 1 month post birth. Hence, the rationale for collecting posttest 1 data during that time. At 3 months post birth is when some working mothers return to work, signifying a change in environment relating to the rational for collecting posttest 2 data. Before contacting parents for the posttest data, a message will be sent to ensure parents’ availability. In the process of data collection, if either parent feels tired, RA2 will respect the parents’ decision to continue or terminate the data collection to ensure parents’ comfort. The consolidated standards of the reporting trial flowchart for this study is presented in Figure 7 [56].

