### Data Analysis

All quantitative data will be analyzed using Statistical Package for the Social Sciences (SPSS) version 24.0 (IBM Corp). Missing data will be replaced (assuming 10%) for intention-to-treat (ITT) analysis. Both ITT analysis and per-protocol analysis will be conducted to compare any differences between groups. Descriptive statistics such as mean, standard deviation, and range for continuous dates, frequencies, and percentages will be used for nominal and ordinal data. Cronbach alpha will be used to test the internal consistencies of the questionnaires. Inferential statistics such as the independent *t* test or ANOVA will be used to compare differences of outcomes between or among demographic subgroups. Presuming that outcomes variables are normally distributed, parametric tests will be used. Repeated measures ANCOVA adjusted for confounding variables will be used to test the effect of intervention on outcome variables across four time points. Univariate ANCOVA will be used to test the differences in outcome variables between two groups at the interim and two posttests data separately.

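### Couples randomised in pregnancy can be excluded for later pregnancy, delivery or newborn events, which is hard to reconcile with the planned intention-to-treat analysis

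*Protocol article*

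**What the plan says.** **Timing.** Under Study Procedure, after consent, "demographic and baseline data of the participants will be obtained, and randomization will take place". Data Collection confirms that the first assessment falls in pregnancy and precedes randomisation. For the intervention group a "telephone-based antenatal education session will be delivered by RA1" then follows, so treatment begins before the birth.

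**Exclusions.** The exclusion textbox for mothers contains criteria that can be met only later: assisted delivery with severe tearing, and having given "birth to a stillborn or a newborn with congenital abnormalities or medical complications". It also lists high-risk pregnancy, including preeclampsia and pregnancy-induced hypertension, which can develop after enrolment. The Participants section shows that these criteria operate after enrolment: couples are recruited antenatally and are told that "they may be excluded from the study if mothers are to experience complication during their pregnancy and the delivery of their newborn".

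**Who knows the allocation.** The first research assistant (RA1) "will be responsible for randomizing the participants" and delivers both telephone-based sessions. Before contact on the postnatal ward, RA1 asks the nurse in charge about the couple's well-being. Blinding, under Data Collection, covers the second assistant (RA2), who collects the interim and later data.

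**Analysis.** Under Data Analysis, "Both ITT analysis and per-protocol analysis will be conducted to compare any differences between groups", and missing data are to be replaced for the ITT analysis, assuming 10%.

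**The concern.** An ITT comparison keeps every randomised couple in the arm to which it was allocated. Here the plan allows couples to leave the study because of events that occur after allocation and, in the intervention arm, after the first session. The primary outcome is parenting self-efficacy, and depression and anxiety are among the others. It is a reasonable assumption, though not one the article documents, that a difficult birth or an ill newborn worsens these scores.

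If such couples are removed more often from one arm, that arm looks better than it should. Adjustment for baseline values cannot repair selection on events that happen later. The number of parents contributing data also falls.

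**Working it through.** **1. Order of events.** Consent, baseline, randomisation, antenatal session (intervention arm), rest of pregnancy, delivery, newborn course. The criteria on assisted delivery, stillbirth and newborn condition are met at the last two steps, and pregnancy complications can arise at the step before them. All of these follow randomisation.

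**2. How fixed the rule is.** Stillbirth and a fourth-degree tear are concrete events. The room for judgement lies in three expressions: *may* in Participants, *such as* in the delivery criterion, and the undefined *medical complications* of the newborn. No decision-maker is named.

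**3. The plan's own figures (Sample Size Determination).** For a two-group ANOVA with f = 0.3 and a two-sided 5% level, the noncentral F has noncentrality N × f² = 90 × 0.09 = 8.1. Power at 45 per group is 0.804, so the stated 45 reproduces. The 30% allowance gives 90 × 1.3 = 117 against the stated 118, a rounding difference that keeps the groups equal. For two equal groups d = 2f = 0.6 SD.

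**4. Bias, by assumption.** The article gives no complication or exclusion rate. Assume that a share p = 0.20 of couples in each arm is complicated, that their outcome is δ SD worse, that there is no true effect, and that a share e of the arm is removed, all from the complicated couples. The mean of those remaining is −δ(p − e)/(1 − e). The spurious difference favours the arm with more removals:

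bias = δ × [(p − e₀)/(1 − e₀) − (p − e₁)/(1 − e₁)], where e₁ is the larger share.

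For 15% v 5% and δ = 0.5: 0.5 × (0.15/0.95 − 0.05/0.85) = 0.5 × (0.158 − 0.059) = 0.050 SD, and 0.05/0.6 is about 8% of the design effect.

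| Removed by arm | δ = 0.5 | δ = 1.0 |
|---|---|---|
| 10% v 10% | 0 | 0 |
| 10% v 5% | 0.02 | 0.05 |
| 15% v 5% | 0.05 | 0.10 |
| 20% v 5% | 0.08 | 0.16 |

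**5. Numbers and power, by assumption.** With the 59 couples of the Abstract, removal of 5% to 20% takes 0.05 × 59 ≈ 3 to 0.20 × 59 ≈ 12 couples. If removals come on top of the 30% attrition, the number left is 118 × (1 − e) × 0.7. Parents are counted as independent here, as in the article's own calculation.

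| Removed | Left | Power at f = 0.3 |
|---|---|---|
| 0% | 82.6 | 0.77 |
| 5% | 78.5 | 0.75 |
| 10% | 74.3 | 0.72 |
| 15% | 70.2 | 0.70 |
| 20% | 66.1 | 0.67 |

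**The case against.** **No contradiction is stated.** Data Analysis does not define the ITT set, does not say that excluded couples leave it, and provides for replacement of missing data. The Participants sentence reports what couples are told and does not define an analysis set. This stands, and the conflict is one of implication. However, exclusion from the study in its ordinary sense ends outcome collection. Replacement would then fill in values for couples whose data were stopped by rule, for a reason plausibly related to the outcome. That is a weak substitute for questionnaires that could have been collected.

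**A reader might infer that an unblinded assistant decides who is removed.** The document does not support this. RA1's question to the nurse in charge reads as a welfare check before contact, is not described as differing by arm, and is not linked to exclusion. What remains is that no one is named to decide, and that the person making the check knows the allocation.

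**A reader might infer that exclusion is wholly discretionary.** *May* can simply mean that nobody yet knows whether a complication will occur, and most criteria are concrete. Only the loose terms leave judgement.

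**A reader might infer that the plan promises an effect for all parents randomised and then narrows it.** No section makes that promise. The hypotheses speak of parents who receive the programme, and the limits to low-risk pregnancy and uncomplicated birth are disclosed.

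**The bias is hypothetical and small.** The only intervention contact planned before delivery is one session of about 30 minutes, which gives little reason to expect removal to differ threefold. With 82.6/2 = 41.3 per arm the standard error of the difference is √(2/41.3) ≈ 0.22 SD, so 0.05 SD is under a quarter of it. The 30% attrition may already cover these losses. All of this stands as a limit on size. It is no reason to leave the rule as it is.

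**Conclusion.** The point holds in a limited form. The plan allows randomised couples to be excluded for pregnancy, delivery and newborn events that follow randomisation. This is hard to reconcile with an ITT analysis and opens a route to selection bias that the design could close.

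The document does not show that such bias will occur. Under the assumptions above it is zero when removal is equal, about 0.05 SD at 15% v 5% with a 0.5 SD deficit, and 0.16 SD in the most extreme case examined. Any loss of power depends on an unstated exclusion rate and on whether the 30% allowance already includes it. The sample size itself reproduces and is not in question here. The sponsor should correct this, but it does not invalidate the trial.

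**What to change.** Reconcile the exclusion textbox, the Participants section and Data Analysis as follows.

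- Apply the eligibility criteria only up to randomisation.
- Keep all randomised couples in follow-up and in the ITT set as allocated, including those with later pregnancy, delivery or newborn complications, unless they decline.
- Name stillbirth as the one exception, because the infant-care outcomes cannot then be measured, and report it by arm. This still conditions on an event after randomisation, so it should be stated openly.
- Use the delivery and newborn criteria only to define the per-protocol set, which is already planned.
- Record any other end of data collection from a fixed list of reasons, judged by someone who does not know the arm, and report it by arm.

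These changes concern follow-up and analysis only. Whether an affected couple continues the programme is a clinical matter and is not addressed here.

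The cost is somewhat more outcome variability, some missing forms from families after a difficult birth, and a few more questionnaires. An ethics and consent amendment is also needed, since Results reports 49 couples already enrolled under the present information.
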